#### Secondary outcome measurements: effects of treatment on psychopathology

There are 10 secondary outcome measures (see Table 1). Firstly, the Posttraumatic Cognitions Inventory (PTCI) is a self-report measure assessing the level of negative thinking an individual has in relation to a specific trauma [43]. Subscales focus on self-blame, along with negative cognitions about the self and the world, which measure trauma-related cognitive distortions. The development and validation study published by the authors reports strong reliability coefficients and convergent validity with other PTSD measures [43].

The Trauma Symptom Inventory—second edition (TSI-2) [44] will be used to assess a broad range of post-trauma symptoms that can arise from acute, early life, and chronic traumatization. The TSI-2 is a 136-item self-report scale with factor analytically derived clinical subscales assessing: anxious arousal, depression, anger, intrusive experiences, defensive avoidance, dissociation, sexual disturbance, impaired self-reference, tension reduction behavior, somatic preoccupation, suicidality, and attachment insecurity. These are collapsed into the four additional factor analytically derived summary scales: self-disturbance, posttraumatic stress, externalization, and somatization. These four factors provide indices of broader complex posttraumatic difficulties beyond the DSM-5 construct of PSTD that may arise from early chronic interpersonal trauma [42]. The TSI also includes two validity scales (which evaluate the tendency to deny common symptoms and over-endorse uncommon symptoms), has extensive general population norms, and has strong psychometric properties [42].

The Beck Depression Inventory—second edition (BDI-II) [45] is a 21-item measure of cognitive, affective, and behavioral symptoms of depression. Items are rated from 0 to 3, with higher scores reflecting more depressive symptoms. The BDI-II is well established, both in international research and in clinical practice. Research supports the use of the BDI-II for screening for depressive disorders in adult mental health patients and is recognized for good internal consistency, retest reliability, and validity [46].

The World Health Organization Disability Assessment Schedule 2.0 (WHODAS 2.0) [47] is a self-report questionnaire that assesses limitations and disability in six domains: cognition; mobility; self-care; getting along with people; life activities, subdivided into household activities and work/school activities; and participation in society. The 12-item version will be used. For each item, respondents rate the level of difficulty experienced, in the prior month, on a 5-point scale from “*none*” to “*extreme or cannot do*”. The WHODAS 2.0 has been found to have good reliability and sensitivity to change across a range of physical and mental health conditions [48].

Psychotic symptoms will be measured by the PSYRATS delusions and hallucinations subscales [49]. The PSYRATS is an instrument that was developed to quantify the severity of delusions and hallucinations. It is commonly used in research studies and clinical settings focussing on people with psychotic illnesses.

Social functioning will be assessed using aspects of the Social Functioning Scale, a measure with sound psychometric properties, established acceptability for patients, and one of the more frequently used social functioning scales in SMI research [50, 51]. It has 79 items covering seven domains of functioning (social engagement/withdrawal; interpersonal communication; pro-social activities; recreation; independence–competence; independence–performance; employment/occupation), with standard scores for each subscale, and an “overall functioning” mean standard score is calculated. For the current trial, a number of questions will be omitted for those residing in secure settings as they are not relevant to that living situation.

Self-esteem will be measured by the Rosenberg Self Esteem Scale (RSES) [52]. This Likert scale has 10 items, each with 4-point scale response options from *strongly disagree* to *strongly agree*. It produces a total ranging from 0 to 30, with scores below 15 considered to reflect low self-esteem. The RSES is likely the most commonly used self-esteem measure in psychology research, and has shown satisfactory validity, reliability, and floor and ceiling effects [53].

To promote participant retention and adherence, we will present information about the study to health professional and patient groups before and during the study, to promote and sustain interest in the trial. We will enlist key worker (case manager) support to remind participants to attend treatment sessions and the follow-up assessments. The therapist and assessors will travel to the site where the participant is residing, to reduce logistical barriers to attending. The EMDR therapist will complete a record of attendance.

Randomized participants who discontinue treatment will have T1 and T2 assessments completed if possible. Once a participant is enrolled, the investigators will make every reasonable effort to follow them up for the entire study period.

#### Subjective experiences of EMDR: qualitative data collection

We are also interested in the subjective experiences of those experiencing PTSD and receiving EMDR treatment, and so this study also contains a qualitative component. We will use in-depth, semi-structured, audio-recorded interviews to explore people’s subjective experiences using a grounded theory approach. Interviews will occur with approximately 10 service users recruited sequentially (until data saturation is reached; *n* + 1) who have undergone EMDR in this trial. Due to the grounded theory study methodology, although there are broad themes and probes, the interviewer will adapt questioning to explore themes raised by the participant rather than sticking rigidly to the initial schedule.

### Sample size calculations

The power is based on information from investigations in related, but not identical, clinical groups to those planned to participate in this trial.

In an RCT investigating EMDR in mental health outpatients with psychosis and PTSD [24], the post-treatment CAPS score for EMDR was 40.3 (*n* = 55), compared with 56.5 (*n* = 47) for the waiting list, a difference of 16 points. The baseline mean (SD) CAPS score for these trial participants was 69.9 (16.2).

A 15-point change in CAPS total severity score has been proposed as a marker of clinically significant change [32], and so we feel that a difference of 16 points on the CAPS is clinically significant, and is likely to represent the difference between severe and moderate symptoms, or moderate and mild (subthreshold) symptoms.

Fifteen participants per arm are needed to detect a change of 16 points with an SD of 16 points using a *t* test and based on equal proportions of participants randomized to each group with a two-sided type I error rate of 0.05 and power of 0.8.

We estimate that attrition could be as much as 30%, although this is likely to be a conservative estimate as a meta-analysis reports that the dropout rate for trauma-focused interventions is around 18% and our previous research in this forensic patient group [29, 54, 55] has found participants to be well engaged with low dropout rates (< 15%). A conservative estimate of dropout is reasonable because the studies in the meta-analysis were over shorter timeframes, and we anticipate that some participants may have been discharged, changed address, or otherwise been lost to follow up at the 6-month mark. Based on the 30% dropout rate, the trial would need to recruit 23 participants per arm.

An important consideration is that we are uncertain whether the SD of the outcome variable will be as previously reported. To this end, we will initially plan to recruit 2 × 8 participants in order to estimate the SD, as the number of participants gives reasonable precision for this estimation. This will also enable us to determine preliminary efficacy, safety, and acceptability data, before further recruiting takes place.

To achieve participant enrolment we will work closely with clinical teams to facilitate targeted enrolment. The Central Regional Forensic Service covers five prisons. We plan to start the trial at two of these sites, selected for practical and representative purposes (one male and one female prison, close to the research center), but if we cannot achieve adequate enrolment at these initial sites, we will add further sites.

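### Fifteen per arm gives 75% power by the stated t test, not 80%; 23 per arm does not follow from 15; and 2 × 8 participants cannot estimate the SD with reasonable precision

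*Protocol article*

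**What the plan says.** The section Sample size calculations in the Protocol article takes its inputs from one earlier trial in outpatients with psychosis and PTSD. Post-treatment CAPS was 40.3 with EMDR, "compared with 56.5 (*n* = 47) for the waiting list, a difference of 16 points". For the spread it gives: "The baseline mean (SD) CAPS score for these trial participants was 69.9 (16.2").

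From these it concludes: "Fifteen participants per arm are needed to detect a change of 16 points with an SD of 16 points". The stated method is a t test with 1:1 allocation, two-sided alpha 0.05 and 80% power.

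It then allows for loss of up to 30%, calls that conservative against about 18% in a meta-analysis and under 15% in the team's own studies, and states: "Based on the 30% dropout rate, the trial would need to recruit 23 participants per arm". The abstract and Table 2 carry this forward as a target of 46.

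The section admits that the outcome SD may differ from the published one. It plans to recruit 2 × 8 participants first to estimate it, "as the number of participants gives reasonable precision for this estimation".

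**The concern.** The section fixes the test, difference, SD, alpha, power and dropout, so each printed number can be checked. Three things fail.

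- The named test does not reach the stated power at the stated number.
- The two printed sample sizes do not connect through the stated dropout.
- The SD, on which power depends most, is a baseline value from participants who all had PTSD, while the comparison is of post-treatment scores, for which the article gives no SD. The check on that assumption is credited with a precision that 16 participants cannot deliver.

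This section is the only justification the article gives for 46. As it stands, a reader cannot derive 46 from it, and may place more trust in the 2 × 8 estimate than it can bear.

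**Working it through.** **Inputs**, all from Sample size calculations: difference 16; SD 16, so d = 16/16 = 1; two-sided alpha 0.05; power 0.80; 1:1 allocation; loss 30%; SD-estimation sample 2 × 8.

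**1. Completers per arm.** Two-sample t test, noncentral t distribution with df = 2n − 2 and noncentrality d√(n/2).

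| n per arm | df | noncentrality | power |
|---|---|---|---|
| 15 | 28 | 2.739 | 75.3% |
| 16 | 30 | 2.828 | 78.1% |
| 17 | 32 | 2.915 | 80.7% |

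So 17 are needed. The normal approximation, n = 2(1.960 + 0.842)²/d² = 15.70, rounds up to 16; at 15 it gives 78.2% power. The printed 15 is therefore not reproduced by either route, and is probably 15.70 rounded down. A one-sided t test would give 84.8% at 15, but the text says two-sided.

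**2. Allowance for loss.** n/(1 − 0.30):

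- 15/0.7 = 21.4, so 22
- 15.70/0.7 = 22.4, so 23
- 16/0.7 = 22.9, so 23
- 17/0.7 = 24.3, so 25

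The stated 23 comes from 15.70 or 16, not from 15.

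**3. Power at the actual target of 46, SD 16.**

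- 30% loss: 23 × 0.70 = 16.1, about 16 per arm, 78.1%.
- 18% loss: 23 × 0.82 = 18.9, about 19 per arm, 85.1%.

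**4. Planned baseline adjustment.** Quantitative data analysis specifies mixed models with the baseline score as covariate. As an approximation, the residual SD is 16√(1 − r²), so d becomes 1/√(1 − r²). The article gives no baseline–outcome correlation r, so these values are assumptions. With 16 per arm:

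- r = 0.3: d = 1.048, power 82%
- r = 0.4: d = 1.091, power 85%
- r = 0.5: d = 1.155, power 88%

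**5. Sensitivity to the SD.** At 16 per arm with an unadjusted t test, an assumed SD of 20 gives d = 0.8 and 59% power. An assumed SD of 24 gives d = 0.667 and 45%.

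**6. Precision of the 2 × 8 estimate.** The pooled within-arm SD has 16 − 2 = 14 df. The 95% interval is s√(14/χ²), with χ² quantiles 26.12 and 5.63:

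- lower: 16√(14/26.12) = 16 × 0.732 = 11.7
- upper: 16√(14/5.63) = 16 × 1.577 = 25.2

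That is −27% to +58%. The t test would need 10 per arm at the lower limit and 41 at the upper. This assumes that all 16 have outcome data. With 10 df left after losses, the interval is 11.2 to 28.1.

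**The case against.** The strongest reply is that the number that matters is 46, not 15. At the worst-case loss, t-test power is 78%, two points short; at the dropout rate cited from the meta-analysis it is about 85%. The planned analysis adjusts for baseline, which an unadjusted t-test calculation leaves out, usually on the cautious side. The 23 exceeds the 22 that 15 would give, so the slip errs in the safe direction, and changing 15 to 16 nearly reconciles the pair. All of this stands, and it is why the point is not a must-fix. It does not make the printed 15 or its link to 23 correct, and the section cannot claim the gain from adjustment while it states a t test and no correlation.

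The article also labels the SD as a baseline value and says openly that the outcome SD is uncertain. That disclosure stands. It makes the precision claim for the check more important, and that claim is not supported.

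A reader might infer that the SD was rounded down from 16.2 to flatter power. The documents do not support this: the difference, 56.5 − 40.3 = 16.2, was rounded in the same way, and 16.2/16.2 and 16/16 both give d = 1.

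A reader might also infer that a chance low SD from the 2 × 8 sample could shrink the trial. The article states no re-sizing rule and nowhere says the target may fall below 46. It says only that the SD will be estimated, alongside preliminary efficacy, safety and acceptability.

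**Conclusion.** The point holds as an error of statement with a small effect on the design; severity should-fix. Three statements are wrong as written: 15 per arm for 80% power (it is 75.3%, and 17 are needed), the step from 15 to 23, and the precision credited to the 2 × 8 sample. The first two follow from the section's own inputs without further assumption. The third rests on the usual chi-square interval for a normal outcome; how wide is too wide is a judgement, but an interval spanning 10 to 41 per arm cannot confirm or refute an SD of 16.

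It would go too far to conclude that a trial of 46 is seriously underpowered. The shortfall is about two points at 30% loss and disappears at the cited 18% or with modest baseline correlation. The 59% and 45% figures depend on SDs of 20 and 24, chosen for illustration; the article does not give the source trial's post-treatment SD, so they show sensitivity and are not a forecast.

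**What to change.** Rewrite the section as follows.

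- State that 17 analysed per arm are needed for 80% power by the t test, and that 46 randomised with 30% loss gives about 78% at SD 16. Alternatively, keep 46 and justify it by the planned baseline-adjusted analysis, with the assumed correlation stated.
- Show power over a range of outcome SDs, and say that 16 is a baseline SD used for want of a post-treatment one.
- Replace the claim of reasonable precision with the interval: 11.7 to 25.2 around an SD of 16 if all 16 participants contribute.
- State that the 2 × 8 SD will not be used to reduce the target below 46. Automatic upward revision from the same estimate is not advised either, because it would rely on the imprecision criticised here and could add participants.

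The cost is the rewording of one section and a slightly less favourable power statement under the t test. No extra participants are needed. Only a wish to keep a full 80% by the unadjusted t test at 30% loss would add any: 25 per arm, 50 in all, which is four more.

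### Fifteen per arm does not give 80% power on the protocol's own inputs: it gives 75%, the named t test needs 17, and 46 recruits with 30% loss give 78%

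*Protocol article*

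**What the plan says.** The section Sample size calculations takes its effect size from an earlier trial of EMDR in outpatients with psychosis and PTSD. The post-treatment CAPS mean there was 40.3 with EMDR, "compared with 56.5 (*n* = 47) for the waiting list, a difference of 16 points". The SD comes from the same trial's baseline: "The baseline mean (SD) CAPS score for these trial participants was 69.9 (16.2").

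The calculation follows: "Fifteen participants per arm are needed to detect a change of 16 points with an SD of 16 points". The test is named as a t test, the allocation is "based on equal proportions of participants randomized to each group", and the error rates are given: "with a two-sided type I error rate of 0.05 and power of 0.8". Attrition is put at up to 30%, a figure the protocol describes as conservative, and the section concludes: "Based on the 30% dropout rate, the trial would need to recruit 23 participants per arm". That makes 46 in total, the figure given in the Abstract and in Table 2.

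**The concern.** Every input needed to check the number is printed in the same paragraph, so nothing has to be assumed. Two things looked wrong.

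- A standardised difference of 1.0 at two-sided 5% and 80% power should need more than 15 per arm with a t test.
- The recruitment figure of 23 does not follow from 15 at 30% loss.

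This is the only power statement in the article. If it is wrong, a non-significant CAPS result will be judged against a power the calculation does not support, and the evaluable and recruited numbers will stand on different bases. The question is separate from whether 16 is a suitable SD or difference for this population.

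**Working it through.** **Inputs (all from Sample size calculations).** Difference 16, SD 16, so d = 16/16 = 1.0. Two-sample t test, equal arms, two-sided alpha 0.05, power 0.80, attrition 30%.

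**1. Attempt to reproduce 15 with the named test.** For n per arm, the power of the t test comes from the noncentral t distribution with df = 2n − 2 and noncentrality d·√(n/2).

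| n per arm | df | noncentrality | critical t | power |
|---|---|---|---|---|
| 15 | 28 | 2.739 | 2.048 | 75.3% |
| 16 | 30 | 2.828 | 2.042 | 78.1% |
| 17 | 32 | 2.915 | 2.037 | 80.7% |

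Solving for 80% gives n = 16.7, so 17 per arm. At 15 per arm the difference detectable with 80% power is 17.0 points, not 16. The printed 15 is not reproduced.

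**2. Other readings of the same paragraph.**

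- Normal approximation: n = 2(1.95996 + 0.84162)² / d² = 15.70, so 16 per arm. Power at 15 is 78.2%.
- Unrounded difference 56.5 − 40.3 = 16.2 with SD 16: t-test power at 15 is 76.3% (normal approximation 79.2%).
- Difference 16 with unrounded SD 16.2: t-test power at 15 is 74.3% (normal approximation 77.2%).
- Both unrounded, 16.2/16.2: d is again 1.0 and the table above applies.
- One-sided t test: 14 per arm, but the protocol specifies two-sided.

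No two-sided reading reaches 80% at 15 per arm.

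**3. The dropout step, n/(1 − 0.30).**

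- 15/0.7 = 21.4, so 22
- 15.7/0.7 = 22.4, so 23
- 16/0.7 = 22.9, so 23
- 17/0.7 = 24.3, so 25 (50 in total)

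The printed 23 fits the normal-approximation result (15.7, or 16 when rounded up). It does not fit the printed 15, nor the 17 that the named test requires.

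**4. Power at the planned size.** 23 × 0.7 = 16.1, so about 16 per arm remain at 30% loss and power is 78.1%. Keeping 17 of 23 (17/23 = 0.739) means a loss of at most 26%, at which power is 80.7%. At 18% loss, the meta-analysis figure the protocol cites, 23 × 0.82 = 18.9, about 19 per arm, and power is 85%.

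**5. Effect of the planned baseline adjustment.** Quantitative data analysis puts the baseline score in the model. For a comparison at one time point, with baseline to post-treatment correlation r, the effective standardised difference is d/√(1 − r²). With 16 per arm:

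| assumed r | effective d | power |
|---|---|---|
| 0.3 | 1.048 | 82% |
| 0.5 | 1.155 | 88% |
| 0.7 | 1.400 | 97% |

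Power passes 80% at r of about 0.22. The document gives no value for r, so these are assumptions.

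**The case against.** The strongest reply is that the error hardly affects the trial as it will be run. The operative number is 46, not 30. At the protocol's own upper bound for attrition that leaves 16 per arm and 78.1% power, 1.9 points short. The 75% figure would apply only if 15 of 23 remained in each arm, a loss of 35%. The protocol calls 30% conservative and cites about 18% from a meta-analysis and under 15% from the team's own studies; at 18% loss power is 85%. The planned analysis adjusts for baseline, which a t test ignores, and a modest correlation would carry 16 per arm past 80%. The first 2 × 8 participants are meant to re-estimate the SD, so any resizing would presumably rerun the calculation instead of carrying 15 forward.

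Most of this stands as a limit on the consequence. It also means the argument that later resizing would inherit the wrong base is weak, and that how 15 arose cannot be known from the document. None of it makes 15 correct. The protocol names a t test, does not invoke baseline adjustment to justify its number, and states 15 and 23 side by side although one does not lead to the other.

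**Conclusion.** The concern holds. On the stated inputs, 15 per arm gives 75.3% power, not 80%; the two-sided t test needs 17; and 15 with 30% loss gives 22 per arm, not 23. This rests on the protocol's own figures alone.

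The printed statement is plainly wrong, but the shortfall at the planned size is small: 78.1% at 46 recruited and 30% loss, and above 80% if loss is 26% or less. Whether baseline adjustment recovers the remaining 1.9 points depends on a correlation the document does not give; about 0.22 would suffice under the single-time-point approximation. It should be corrected because it is the trial's only power statement and the correction is easy, not because the trial is seriously underpowered on these inputs.

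**What to change.** Reword the calculation in Sample size calculations in one of two ways.

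1. **Keep the t test.** State that 17 evaluable participants per arm are needed for 80% power. Then state that 46 recruited gives about 78% power at 30% loss (16 per arm) and at least 80% if loss is 26% or less. To hold 80% at 30% loss with this test, the target would be 25 per arm, 50 in total.
2. **Use the planned model.** Base the power statement on the baseline-adjusted comparison, with the correlation declared as an assumption and a range shown: for 16 per arm, 82%, 88% and 97% at 0.3, 0.5 and 0.7.

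In both cases the evaluable number, the attrition allowance and the recruitment number should follow from one another. With the target left at 46, the cost is wording only: no extra participants and no change to the design or analysis. Under the first option the stated power becomes slightly less favourable, 78% in place of 80%.

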### Trial monitoring and oversight

The risks of the study are thought to be low based on previous research, which has found EMDR to be safe, effective, and well tolerated in people with serious mental illness. However, the population is vulnerable so there are a number of safeguards in place. A Data Monitoring Committee (DMC) has been set up as an advisory body responsible for monitoring emerging safety and efficacy data, reviewing trial conduct and making recommendations. The DMC is independent of the study organizers and funders. Its membership is multidisciplinary and comprises the Clinical Director (Chair) and Operations Manager from the Central Regional Forensic and Rehabilitation Service, a senior psychologist not related to the study, and the principal investigator. During the recruitment period, interim analyses will be supplied in strict confidence to the DMC, together with any analyses the DMC may request.

The base rate of serious events in this population is much higher than in the general population, and it may be difficult to establish whether such events are related or unrelated to therapy. All serious adverse outcomes will be reported immediately to the DMC. We have predetermined that any serious event such as a serious deliberate self-harm attempt (requiring medical attention), an assault on another person (requiring medical attention), or a return to an environment of high security will be a reason for the participant being withdrawn from the study. Any other significant adverse effects will be discussed on a case-by-case basis. The DMC and research team will formally review the feasibility and safety of the study after data have been collected on 10 participants, before further participants are recruited.

The terms of reference of the DMC are available on request from the principal investigator.

In the unlikely event that someone is harmed in the course of the trial, they would be eligible under New Zealand law to apply for compensation from the Accident Compensation Corporation. This is explained in the informed consent process.

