### Quantitative data analysis

Data analyses will be performed by a biostatistician blinded to treatment allocation using intention-to-treat and per-protocol analyses. The per-protocol analysis group refers to those participants who completed the treatment as originally allocated. We have defined this as participants who undergo at least six of the maximum nine total number of EMDR treatment sessions or who fulfill the criteria for early completion.

Baseline differences in demographic and clinical characteristics between the EMDR and control group will be analyzed using chi-squared tests, *t* tests, and analysis of variance. Descriptive statistics will provide data summaries. Continuous variables will be analyzed on an intention-to-treat basis with linear mixed models. For the PSYRATS data, which is usually not normally distributed because of a disproportionate number of zero scores, differences will be analyzed using the Wilcoxon signed-rank test and the Mann–Whitney *U* test.

Baseline scores will be included as covariates, time as a categorical variable, and treatment condition as a fixed effect. The intercept will be treated as a random effect. Dichotomous outcomes will be analyzed with logistic generalized estimating equation analyses with exchangeable correlation structure.

Effects will be calculated for post treatment and 6-month follow-up using interaction effects. Analyses of completers and intent-to-treat analyses with the last observation carried forward (with missing data on loss of diagnosis conservatively replaced with a negative value, i.e., no loss of diagnosis) will be performed to test the robustness of the findings.

The number needed to treat will be calculated to determine the number of participants who needed to be treated to make one more patient lose the PTSD diagnosis or achieve full remission compared with the control condition.

All tests will be two-sided and *p* < 0.05 will be considered statistically significant. We will use multiple imputations for missing data.

A biostatistician is part of the research team.

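### The 2 × 8 first stage is worded to give the research team an efficacy look before further recruitment, with no decision rule; this conflicts with the confidential route to the DMC and can inflate type I error

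*Protocol article*

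**What the plan says.** Under Sample size calculations, the plan is sized on a t test: "Fifteen participants per arm are needed to detect a change of 16 points with an SD of 16 points", with "equal proportions of participants randomized to each group with a two-sided type I error rate of 0.05 and power of 0.8". Attrition then sets the target: "Based on the 30% dropout rate, the trial would need to recruit 23 participants per arm", which is 46 in total. Because the SD is uncertain, "we will initially plan to recruit 2 × 8 participants in order to estimate the SD". The next sentence gives the stage a second use: "This will also enable us to determine preliminary efficacy, safety, and acceptability data, before further recruiting takes place".

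Under Trial monitoring and oversight, the route is different: "During the recruitment period, interim analyses will be supplied in strict confidence to the DMC, together with any analyses the DMC may request". The same section has the DMC and the research team review feasibility and safety together once data exist on 10 participants, again before more are recruited. It also lists the principal investigator among the DMC's members.

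Under Quantitative data analysis, the level is plain: "All tests will be two-sided and *p* < 0.05 will be considered statistically significant". The analyst is described there, and in the randomization section, as blinded to allocation.

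**The concern.** The uncertainty that motivates the first stage concerns the SD, and that can be resolved without comparing arms. Preliminary efficacy against a waiting list cannot. The sentence therefore adds a between-arm look that the SD estimate does not need, assigns it to the authors' own team, and places it just before a recruitment decision, without saying what the result may change.

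Two things are at stake:

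- **Exposure.** Investigators meet candidates, take consent, may withdraw participants and follow up those who discontinue. Knowing the interim difference could colour those judgements for the remaining 46 − 16 = 30 participants.
- **Error rate.** If the sample size or the decision to continue responds to the observed difference, a final test at 0.05 that includes the first 16 no longer has a 5% false-positive rate.

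**Working it through.** **The plan's own size.** With a difference of 16, SD 16, two-sided 0.05 and power 0.80, the normal approximation gives n = 2(1.960 + 0.842)² × 16²/16² = 15.7, so 16 per arm; the exact t test needs 17. The stated 15 is close to both. 16/0.7 = 22.9, so 23 per arm, as stated.

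**Side by side.**

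| | Sample size section | Monitoring section |
|---|---|---|
| Participants at the look | 16 (2 × 8) | 10 for the joint review |
| Content | SD, efficacy, safety, acceptability | Joint review: feasibility and safety |
| Who learns of efficacy | the authors' team | the DMC, confidentially |
| Rule for efficacy | none | none |

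**Do the 16 count?** No sentence says so. They are recruited first towards 23 per arm, the analysis is by intention to treat, and nothing sets them aside, so inclusion is the natural reading.

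**Type I error.** These are simulations under no difference (two-sample t tests, 100,000 to 400,000 trials per setting), with the first 8 per arm kept in the final test at 0.05. Where the size is reset, n = 15.70 × s²/16², where s is the first-stage SD. True SDs from 12 to 25 are used because an SD of 16 estimated on 14 degrees of freedom has a 95% interval of 11.7 to 25.2.

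| Use made of the look | Type I error |
|---|---|
| Success may be claimed at 8 per arm or at the end (15, 16, 23 per arm) | 8.3%, 8.5%, 8.8% |
| Size reset up or down on within-arm SD | 5.4–6.1% |
| Size reset on within-arm SD, minimum 23 per arm | 5.0–5.2% |
| Size reset on pooled SD without arm labels | 4.9–5.1% |
| Stop only if the effect is in the wrong direction | 2.5% |

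**Checking the remedy.** All figures use the pooled SD without arm labels.

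- *Planned 16-point difference subtracted, no minimum size:* type I error stays at 0.05, but power at a true 16-point difference is only 71–76% for SDs of 12 to 25 (71% at SD 16).
- *No subtraction, minimum 23 per arm, all evaluable:* type I error is 0.049–0.050. Power is 99%, 92%, 83% and 78–79% at SDs of 12, 16, 20 and 25.
- *No subtraction, minimum 16 evaluable per arm (23 × 0.7 = 16.1):* type I error is 0.049–0.050. Power is 96%, 85%, 80% and 78% at the same SDs.

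**The case against.** A fair reply would be that the only decision purpose stated for the stage is to estimate the SD. There is no efficacy stop, no early claim of success and no change of size based on the observed difference. The wording may be loose authorial style for results that the trial obtains through the DMC, which is charged with monitoring efficacy as well as safety. The statistician is blinded. Outcome assessors are blinded too, and an unblinded assessment is repeated by someone else. Interim rules may also sit in the DMC's terms of reference, which are available on request.

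Much of this stands. A reader might infer that the trial will run at a false-positive rate near 9%; the text does not support that, because it states no stop for success. That the team sees results by arm is likewise an inference, since efficacy can hardly be determined otherwise, but the text does not spell it out. Blinded assessment protects CAPS ratings, and an aggregate difference reveals nobody's allocation, so biased scoring of individuals is not a supported claim.

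What does not fall away is the published sentence itself. It announces an efficacy result for the team before recruitment continues, and that does not fit with a confidential DMC route and a joint review confined to feasibility and safety. This is a conflict in what is written, not a detail left to another document.

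**Conclusion.** The point holds as a conflict to be resolved and a conditional risk. The exposure of the team is the firmer part; it follows from reading the two sections together. The effect on type I error depends on a use of the look that the protocol leaves open: about 8.5–9% if success could be claimed at 2 × 8 and recruitment otherwise ran to 16–23 per arm, about 5–6% if the size is reset on the within-arm SD (nearer 5% with 23 per arm as a minimum), and no inflation with a blinded SD or a look used only for safety or futility. All figures assume normally distributed scores with equal variances, a t test as in the sample size section, and that the first 16 stay in the final analysis.

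**What to change.** Replace the sentence under Sample size calculations with text to this effect:

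- After the first 16 participants reach the post-treatment CAPS, the SD is estimated from pooled data without arm labels and without subtracting the assumed difference.
- On that figure alone the size may be raised, never lowered, from 23 per arm. The revised evaluable number carries the same 30% allowance.
- No between-arm efficacy comparison is made for or shown to the research team, and recruitment does not depend on efficacy.
- Arm-level safety data go to the DMC only. Because the principal investigator is listed as a member, say how those data are kept from that role.
- The first 16 stay in the final analysis at two-sided 0.05.

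Reconcile this stage with the 10-participant review in the monitoring section. Recruitment began in May 2018, so if the look has already taken place, report what was seen, by whom, and whether size or continuation depended on it.

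If an efficacy look is wanted after all, it needs a stated boundary and should go to the DMC, not the team. At 8/23 of the information, O'Brien–Fleming-type spending gives p < 0.0009 at the look and p < 0.0498 at the end.

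The cost is mainly wording. The team gives up an early impression, which would be weak anyway: 8 evaluable per arm give 46% power for the planned effect. The pooled SD also overstates the within-arm SD if EMDR works: with a 16-point difference and SD 16, √(256 + 64 × 16/15) = 18.0. Counting all 23 per arm as evaluable, mean size at SD 16 is 24.8 per arm against 23.5 with the within-arm SD. With a minimum of 16 evaluable it is 21.4 against 18.4, or about 31 against 26 recruited per arm after dividing by 0.7.
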